# Qizhi Jieyu Pill for the Treatment of Cerebral Infarction During the Recovery Phase: Protocol for a Randomized Controlled Clinical Trial

**DOI:** 10.2196/75982

**Published:** 2025-08-13

**Keywords:** cerebral infarction, recovery phase, Qizhi Jieyu pill, clinical research, study protocol

## Abstract

**Background:**

Cerebral infarction, a life-threatening neurodegenerative disease, is one of the leading causes of disability and death. The recovery phase is a critical period for patients to regain cognitive ability, memory, and motor functions and to improve their ability to perform daily activities. Over the past 10 years, we have applied Qizhi Jieyu pill in the treatment of patients in the recovery phase of cerebral infarction. We retrospectively analyzed clinical data from 152 patients and found preliminary results suggesting that Qizhi Jieyu pill may help alleviate clinical symptoms, improve quality of life, and reduce the recurrence of cerebral infarction. However, the lack of high-quality clinical evidence supporting its efficacy and safety has limited its widespread clinical application.

**Objective:**

This protocol describes a randomized controlled trial aiming to evaluate the efficacy and safety of Qizhi Jieyu pill in patients during the recovery phase of cerebral infarction.

**Methods:**

This study adopts a multicenter, randomized controlled clinical trial design. A total of 126 patients aged 30-70 years in the recovery phase of cerebral infarction will be recruited and randomly assigned in a 1:1 ratio to either the study group (n=63, receiving conventional treatment plus Qizhi Jieyu pill) or the control group (n=63, receiving conventional treatment alone). The intervention period will last 12 weeks, and the total follow-up period will be 48 weeks. The primary outcome is the change in the National Institutes of Health Stroke Scale score at week 48. Secondary outcomes include changes in traditional Chinese medicine syndrome scores, the recurrence rate of cerebral infarction, and modified Rankin Scale scores. Adverse events will be recorded and used to assess the safety profile. All data analyses will be performed according to a prespecified statistical analysis plan.

**Results:**

The study received ethics approval on March 3, 2025, from the Ethics Committee of Guang’anmen Hospital, China Academy of Chinese Medical Sciences (2025-025-KY-01) and was registered on April 6, 2025. Participant recruitment began on April 10, 2025, and is expected to be completed by December 31, 2025. Final results will be published by December 31, 2026.

**Conclusions:**

This study is the first randomized controlled clinical trial to evaluate the efficacy and safety of Qizhi Jieyu pill in the treatment of patients during the recovery phase of cerebral infarction. It will contribute to the development of integrated treatment strategies, potentially leading to broader clinical adoption, by providing a high-quality, evidence-based treatment option for clinical practice.

**Trial Registration:**

International Traditional Medicine Clinical Trial Registry ITMCTR2025000653; https://itmctr.ccebtcm.org.cn/mgt/project/view/2028021950497347405/false

**International Registered Report Identifier (IRRID):**

PRR1-10.2196/75982

## Introduction

Cerebral infarction, a life-threatening neurodegenerative disease, predominantly affects older adults and is classified as an ischemic cerebrovascular event [1]. Due to the various degrees and types of brain damage it causes—such as brain tissue lesions, structural damage, neuronal death, and dysfunction—it remains one of the leading causes of disability and death [2,3]. According to the 2019 Global Burden of Disease study, the age-standardized incidence rate of cerebral infarction in China was 144 per 100,000, and the age-standardized prevalence was 1255.9 per 100,000. With the acceleration of population aging, the burden of this disease is expected to continue rising [4].

The acute phase of cerebral infarction progresses rapidly, with most patients entering the recovery phase approximately 2 weeks after onset, which typically lasts about 6 months. The recovery phase is crucial for regaining cognitive ability, memory, and motor functions, thereby enhancing daily living capabilities. Hence, rehabilitation during this stage is a hot topic in clinical research [5]. Core treatment strategies during this phase primarily include antiplatelet therapies, such as aspirin, clopidogrel, sarpogrelate, and cilostazol, aimed at reducing stroke recurrence and improving neurological function [6-8]. However, these treatments have yet to effectively address the high recurrence and disability rates.

Multiple clinical studies have confirmed that traditional Chinese medicine (TCM) therapies—such as Buyang Huanwu decoction and acupuncture—can significantly improve clinical symptoms during the recovery phase of cerebral infarction. These include reducing the recurrence rate of cerebral infarction, enhancing neurological function, and mitigating the severity of neurological deficits, making TCM a vital component of stroke rehabilitation [9-14].

We have used Qizhi Jieyu pill, composed of traditional herbs such as *Panax notoginseng* and leech, in clinical practice for over 10 years to treat patients during the recovery phase of cerebral infarction. Preliminary, retrospective analysis of 152 cases indicates that Qizhi Jieyu pill may alleviate clinical symptoms, improve quality of life, and reduce recurrence. This suggests its potential as an important therapeutic option during the recovery phase. However, there is still a lack of high-quality clinical studies to validate its efficacy and safety.

This study aims to evaluate the efficacy and safety of Qizhi Jieyu pill in the treatment of patients during the recovery phase of cerebral infarction through a randomized controlled clinical trial. We hypothesize that the addition of Qizhi Jieyu pill to conventional treatment will result in greater improvement in National Institutes of Health Stroke Scale (NIHSS) scores and lower recurrence rates compared to conventional treatment alone.

## Methods

### Study Design

This study aims to evaluate the efficacy and safety of Qizhi Jieyu pill in the treatment of cerebral infarction during the recovery phase. It adopts a multicenter, randomized controlled clinical trial design and will be conducted in accordance with the principles of the Declaration of Helsinki, the Good Clinical Practice guidelines, and Chinese regulations. The study will be carried out at Guang’anmen Hospital, China Academy of Chinese Medical Sciences, and Wuzhai County Hospital of Traditional Chinese Medicine.

### Ethical Considerations

The Ethics Committee of Guang’anmen Hospital of the China Academy of Chinese Medical Sciences approved the study (2025-025-KY-01). All patients provided their written informed consent to participate in the study and authorized the publication of their data. The trial has been registered with the International Traditional Medicine Clinical Trial Registry (ITMCTR2025000653).

### Sample Size Calculation

The clinical sample size was calculated using a 2-group mean difference test (shown below), where n is the required sample size per group, σ is the pooled SD of the 2 groups, α is the type 1 error, β is the type 2 error, and δ is the expected mean difference between the study and control groups.

Since there are currently no direct data available to calculate the clinical sample size, we mainly referred to 2 clinical studies [15,16]. In these studies, the NIHSS score change value in the control group (conventional treatment) was approximately 4.9. The pooled SD (σ) was estimated based on prior studies that reported SDs ranging from 1.5 to 2.5. We conservatively used σ=2.0 in our calculation to ensure adequate power. It is hypothesized that the change in the study group (conventional treatment plus Qizhi Jieyu pills) would be approximately 6, with a mean difference of 2 between the 2 groups. Assuming a 1:1 sample ratio between the control and study groups with α=0.05 and β=0.2, the required sample size per group is 52. Considering an overall dropout rate of 20%, each group needs 63 participants, for a total of 126 participants. A third-party group composed of experts in TCM, endocrinology, and statistics will be organized at the midterm of the study to reassess the sample size based on the observed effect size of the primary efficacy indicators and associated errors. Figure 1 shows the study flowchart.

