### Outcomes

#### Primary Outcome

The primary outcome is the change in NIHSS score at 48 weeks [21]. This scale evaluates levels of consciousness, command compliance, eye movement, visual field defects, facial paralysis, limb motor dysfunction, ataxia, speech expression, and other parameters.

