#### Statistical Analysis Plan

A statistical analysis plan was formulated prior to the start of the study. It will be finalized after discussion among the statisticians, principal investigators, and sponsor before database lock. This plan describes only the standard statistical requirements.

Statistical analysis will be conducted using SAS version 9.4. All hypothesis tests will be 2-sided, with a significance level of α=.05. *P* values less than or equal to .05 will be considered statistically significant.

For continuous variables, mean, SD, minimum, maximum, and median values will be used for descriptive statistics. Independent samples *t* tests (for normally distributed data) or Wilcoxon rank-sum tests (for non-normally distributed data) will be used for hypothesis testing. Normality of continuous variables will be assessed using the Shapiro-Wilk test before choosing appropriate parametric or nonparametric tests.

For categorical variables, frequency and percentages will be used for description. Chi-square tests or Fisher exact tests will be used for hypothesis testing. Ordinal variables will be analyzed using the Wilcoxon rank-sum test.

Logistic regression will be used to control for confounding factors affecting the outcome measures. We will also analyze the association between syndrome evolution patterns and therapeutic efficacy. In parallel, multivariate linear regression will be used to explore the relationship between outcomes and potential confounders, such as baseline NIHSS score, study center, age, and sex. For adverse events potentially associated with animal-derived components—including itching, rash, allergic reactions, and gastrointestinal discomfort—we will conduct attribution analysis and report their incidence separately.

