### Comparison to Prior Work

Compared with prior clinical trials evaluating TCM interventions, such as Tiandan Tongluo capsule [16] and Yindan Xinnaotong soft capsule [15], for poststroke rehabilitation, our study exhibits several innovative features. First, it adopts a longer follow-up period of 48 weeks, enabling a more comprehensive assessment of long-term outcomes such as recurrence and disability. Second, it incorporates a broader inclusion framework without limiting to specific TCM syndrome types, thus improving generalizability. Third, the outcome evaluation uses a dual-system framework that combines biomedical scales (NIHSS and modified Rankin Scale) with standardized TCM syndrome scores, thus enhancing the clinical interpretability of integrative medicine. Finally, our trial is grounded in over a decade of practical experience with Qizhi Jieyu pill and is the first to systematically evaluate this compound through a rigorously designed randomized controlled trial supported by mechanistic insights from pharmacological research.

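### The SD of 2.0 described as conservative is the midpoint of the protocol's own range; at the difference that reproduces 52 per group, SD 2.5 leaves about 60% power

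*Protocol article*

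**What the plan says.** All planning values stand in one paragraph of the protocol article, Sample Size Calculation. The authors say that they had no direct data and relied mainly on two cited clinical studies.

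- **Control-arm change in NIHSS:** "In these studies, the NIHSS score change value in the control group (conventional treatment) was approximately 4.9".
- **Study-arm change:** about 6, given as a hypothesis of this trial.
- **Difference between groups:** written as 2.
- **SD:** based on "prior studies that reported SDs ranging from 1.5 to 2.5". The value used is 2.0, which the text calls a conservative choice made so that power would be adequate.
- **Result:** "Assuming a 1:1 sample ratio between the control and study groups with α=0.05 and β=0.2, the required sample size per group is 52". This is raised to 63 per group for 20% dropout.

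The Statistical Analysis Plan section fixes the sidedness: "All hypothesis tests will be 2-sided, with a significance level of α=.05". The Primary Outcome section fixes the time point: "The primary outcome is the change in NIHSS score at 48 weeks". The Comparison to Prior Work section names the two trials that supplied the 4.9 and contrasts this trial with them: "First, it adopts a longer follow-up period of 48 weeks, enabling a more comprehensive assessment of long-term outcomes such as recurrence and disability".

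**The concern.** In a comparison of two means, the required sample size grows with the square of the SD. A conservative SD is therefore one near the top of the plausible range. The protocol gives a range and takes its centre, so the claim of conservatism is wrong on the protocol's own figures.

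How much this matters depends on the difference assumed, and here the paragraph contradicts itself: 6 minus 4.9 is 1.1, not 2. If 1.1 is the basis, the SD choice decides whether the trial has about 80% or about 60% power. If 2 is the basis, power is high at any SD in the range, but the stated 52 does not follow.

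A reader who trusts the word conservative would take a non-significant week-48 result as coming from a trial with at least 80% power. On the protocol's own upper SD, that reading would be too strong.

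A smaller matter is that the control-arm value comes from trials which the article implies were followed for less time, while the endpoint is at week 48. The article does not say that the difference is assumed to hold at that time.

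**Working it through.** **Inputs.** α = 0.05 two-sided (Statistical Analysis Plan section); power 80%, 1:1 allocation, control change 4.9, study change 6, written difference 2, SD range 1.5 to 2.5, SD used 2.0, n = 52 per group (all Sample Size Calculation).

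**Formula.** Normal approximation for two means: n per group = 2 × (1.96 + 0.8416)² × σ² / δ² = 15.70 × σ² / δ².

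**1. Reproduce the stated 52.**

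- δ = 6 − 4.9 = 1.1, σ = 2.0: 15.70 × 4 / 1.21 = 51.9, so 52. This matches. (An exact t calculation gives 53.)
- δ = 2, σ = 2.0: 15.70 × 4 / 4 = 15.7, so 16 (17 by t). This does not match.

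The stated sample size therefore rests on 1.1, and the written 2 was not used to obtain it.

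**2. Where 2.0 lies in the quoted range.** (1.5 + 2.5) / 2 = 2.0, the exact midpoint.

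**3. Sample size for 80% power at δ = 1.1 across the range.**

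- σ = 1.5: 15.70 × 2.25 / 1.21 = 29.2, so 30 per group.
- σ = 2.0: 52 per group.
- σ = 2.5: 15.70 × 6.25 / 1.21 = 81.1, so 82 per group (83 by t).

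**4. Power of 52 per group.** Power = Φ(δ / (σ√(2/n)) − 1.96), with √(2/52) = 0.1961.

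- δ = 1.1, σ = 2.0: 1.1 / 0.3922 = 2.804; Φ(0.844) = 80.1%.
- δ = 1.1, σ = 2.5: 1.1 / 0.4903 = 2.244; Φ(0.284) = 61.2%.
- δ = 2, σ = 2.5: 2 / 0.4903 = 4.079; Φ(2.119) = 98.3%.

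| Difference | SD | Power, normal approximation | Power, noncentral t |
|---|---|---|---|
| 1.1 | 1.5 | 96.2% | 95.9% |
| 1.1 | 2.0 | 80.1% | 79.3% |
| 1.1 | 2.5 | 61.2% | 60.4% |
| 2 | 2.5 | 98.3% | 98.1% |

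**5. Week 48.** No calculation is possible. The article gives neither the follow-up length of the two cited trials nor the time at which 4.9 was measured, and it gives no week-48 effect or SD from any source.

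**The case against.** **The written difference is 2, and at 2 the SD hardly matters.** This is the strongest reply. With 52 per group, power at a difference of 2 is 98% even at SD 2.5. But a difference of 2 at SD 2.0 needs only about 16 per group, so it cannot be the basis of 52. The 79 to 80% and 60% figures apply to the difference that yields the published sample size. The contradiction has to be settled before any power figure is restated.

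**A midterm reassessment is planned.** The same paragraph provides for a third-party group to revisit the sample size using the observed effect and its error. This softens the risk from a wrong SD. It does not make the midpoint a conservative choice.

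**More than 52 per group may be analysed.** The full analysis set keeps participants with one post-baseline efficacy evaluation and carries the last value forward. If all 63 per group were analysed at a difference of 1.1, power by the normal approximation would be 87% at SD 2.0 and 69% at SD 2.5. The latter is still below 80%.

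**The week-48 argument can be pushed too far.** A reader might infer that the 80% belongs to an earlier endpoint, that the study-arm value of 6 is a short-term result, or that the endpoint has two time points. The documents support none of these. Only the 4.9 comes from the cited trials, and the 6 is this trial's own hypothesis. The time at which the 4.9 was measured is not stated. The abstract and the Primary Outcome section both give week 48 alone. Any figure for partial fading of the effect would have no input from the documents. Planning from shorter studies when nothing better exists is an ordinary assumption. What stands is only that it should be stated.

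**Conclusion.** The claim that the SD was chosen conservatively is wrong: 2.0 is the middle of the protocol's own range. At the difference that reproduces 52 per group, power is 79 to 80% at SD 2.0 and about 60% at SD 2.5, where about 82 per group would be needed for 80%. The written difference of 2 conflicts with 6 minus 4.9 and does not yield 52.

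These figures rest on a two-sided 5% test, 52 evaluable participants per group, an equal SD in both groups and a true difference of 1.1. They do not show that the trial is underpowered, because the documents do not show that the true SD is 2.5. They show that the stated margin of safety is absent.

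The follow-up point is secondary: the assumption that the hypothesized difference holds at week 48 is unstated, and neither the size nor the direction of any error can be derived.

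**What to change.** In the Sample Size Calculation section:

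1. Reconcile the stated difference of 2 with the 1.1 implied by 6 and 4.9, and say which one the 52 per group rests on.
2. Delete the description of SD 2.0 as conservative and call it the midpoint of the reported range.
3. Report power at SD 2.5 (about 60% with 52 per group at a difference of 1.1) beside the SD 2.0 figure.
4. Add one sentence saying that the control change of 4.9 comes from trials whose follow-up the Comparison to Prior Work section implies was shorter, and that the power figure assumes the hypothesized difference holds at week 48.

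The cost is a few lines of text and a less favourable power statement. Enrolment, design and analysis stay as they are.

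### The sample-size paragraph states a target difference of 2, but its own arm values differ by 1.1, and 52 per group follows from 1.1

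*Protocol article*

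**What the plan says.** All the design inputs stand in one paragraph, Sample Size Calculation:

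- Control arm: "the NIHSS score change value in the control group (conventional treatment) was approximately 4.9".
- Study arm: the change "would be approximately 6, with a mean difference of 2 between the 2 groups".
- Variability: the SD is drawn from "prior studies that reported SDs ranging from 1.5 to 2.5", and then "We conservatively used σ=2.0 in our calculation to ensure adequate power".
- Error rates: "Assuming a 1:1 sample ratio between the control and study groups with α=0.05 and β=0.2". The Statistical Analysis Plan section adds "All hypothesis tests will be 2-sided, with a significance level of α=.05".
- Result: "the required sample size per group is 52".
- Inflation: "Considering an overall dropout rate of 20%, each group needs 63 participants, for a total of 126 participants".

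The same paragraph announces a midterm reassessment of the sample size, made by a third-party group from the observed effect size and its error.

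**The concern.** The paragraph defines δ as the expected mean difference between the groups and then gives it two values. One is explicit (2). The other is implied by the arm values (6 − 4.9 = 1.1). They differ by a factor of about 1.8, and because n varies with 1/δ² they imply sample sizes that differ by a factor of more than three.

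The consequence is practical. The midterm group is to compare what has been observed with what was assumed. As printed, it could take either 1.1 or 2 as the assumed effect and reach quite different conclusions about whether 126 participants are enough. A reader also cannot tell which effect the trial was sized to detect.

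Two further statements in the paragraph do not match their own figures: the step from 52 to 63 for 20% dropout, and the description of SD 2.0 as conservative.

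**Working it through.** **Formula.** The article's displayed formula is not in the text available, so I used the standard one for two means, n per group = 2σ²(z₁₋α/₂ + z₁₋β)²/δ². For two-sided 0.05 and 80% power, (1.960 + 0.842)² ≈ 7.849.

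**Step 1: reproduce the 52.** With σ = 2.0, the numerator is 2 × 4 × 7.849 = 62.79.

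- δ = 1.1: 62.79/1.21 = 51.9, so 52. This matches the article.
- δ = 2: 62.79/4 = 15.7, so 16. This does not.

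**Step 2: can any reading of δ = 2 give 52?**

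| Reading with δ = 2 | n per group |
|---|---|
| SD 1.5, two-sided | 9 |
| SD 2.0, two-sided | 16 |
| SD 2.5, two-sided | 25 |
| SD 2.0, one-sided | 13 |

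Reaching 52 with δ = 2 would need σ = √(52 × 4/(2 × 7.849)) = 3.64, outside the quoted range. With δ = 2 and SD 2.0, 52 per group would have about 99.9% power.

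Rounding does not help either. If 4.9 stands for at least 4.85 and 6 for at most 6.5, the largest possible difference is 1.65.

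**Step 3: dropout inflation.** 52 × 1.2 = 62.4, so 63, which is the article's figure. To keep 52 after losing 20%, the divisor is 0.8: 52/0.8 = 65 per group, 130 in total. With 63 per group, 52 remain only if at most 11 are lost, and 11/63 = 17.5%. At 20% loss, 63 × 0.8 = 50.4 remain.

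**Step 4: power at 50 per group, δ = 1.1.** By the normal approximation, power = Φ(δ/(σ√(2/n)) − 1.960), with √(2/50) = 0.2.

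| SD | δ/(σ × 0.2) | Power, normal approximation | Power, t test |
|---|---|---|---|
| 1.5 | 3.67 | 95.6% | 95.3% |
| 2.0 | 2.75 | 78.5% | 77.7% |
| 2.5 | 2.20 | 59.5% | 58.6% |

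With 50.4 per group and SD 2.0 the figures are 78.8% (normal) and 78.1% (t test). For comparison, 52 per group gives 80.1% by the normal approximation, the method that reproduces the article's 52, and 79.3% by the t test, which would need 53.

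**Step 5: the SD.** (1.5 + 2.5)/2 = 2.0, so the chosen value is the midpoint. At SD 2.5 and δ = 1.1, n = 2 × 6.25 × 7.849/1.21 = 81.1, so 82 evaluable per group.

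**The case against.** The strongest reply is that the sample size is right and only one printed number is wrong. That stands. The 52 reproduces from the arm values, so the calculation was evidently not made with 2. A reader might infer that the trial was sized for the wrong effect, or that 52 is a mistake; the documents do not support either.

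The next reply is that the dropout step is small. That also stands: two participants per group, and about 1.2 to 1.5 points of power by the article's own type of formula. A reader might go further and infer that 80% power is simply not met under the plan's 20% dropout. The documents do not support that without a condition. Under Definition and Selection of Statistical Analysis Datasets, the full analysis set keeps every randomized participant with at least one postbaseline efficacy evaluation and carries the last observation forward for the primary outcome. The section on participant withdrawal likewise uses the last recorded results. Someone who leaves after the week-12 visit therefore stays in the analysis; only those without that first evaluation are lost. Carrying values forward may alter the difference or the SD, but the documents give nothing from which to quantify that.

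On the SD, 2.0 is a permissible assumption and not a wrong figure; only its description is at fault. The 59% at SD 2.5 combines the top of the quoted range with full loss of 20%. It should not be read as the expected power, since the same calculation gives about 95% at SD 1.5 and the midterm reassessment may respond to a larger SD.

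Finally, a reader might take δ as the yardstick for the final result. The analysis section judges results by two-sided P values; δ serves the design and, by implication, the midterm reassessment.

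**Conclusion.** The contradiction between the stated difference of 2 and the implied difference of 1.1 is real and must be corrected. Rounding and choice of method do not explain it: with the stated SD, alpha and power, 1.1 gives 52 per group and 2 gives 16. That 1.1 was the working value is an inference from the exact match, and the investigators should confirm it.

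The other two points are minor. The inflation to 63 falls two per group short of 65, and power for a difference of 1.1 at SD 2.0 is about 78–79% instead of 80%, on the assumption that a full 20% contribute no primary outcome data. The word conservatively misdescribes a midpoint. Neither point shows that the trial is inadequately sized.

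**What to change.** 1. State the target difference as 1.1 (6 − 4.9). If 2 was intended, correct the arm values and recompute n. Settle this before the midterm reassessment, so that it works from one assumed effect.
2. Keep 126. State that 63 per group gives about 78–79% power at a difference of 1.1 and SD 2.0 if 20% contribute no primary outcome data, that 52 evaluable per group are kept only up to 17.5% loss, and that last observation carried forward may retain some dropouts.
3. Delete the word conservatively and show power across the quoted SD range: with 50 per group, about 95% at SD 1.5, 78% at 2.0 and 59% at 2.5 (t test).

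If 1.1 is confirmed, the cost is a few words and one short power statement, with no extra participants and no change to the analysis. The stated power becomes slightly less favourable. Only the article is at hand; if the same sentence stands in the full protocol or the registry entry, it needs the same correction there.

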#### Trial Termination Criteria

Satisfaction of any of the following criteria will result in discontinuation of the clinical trial before the planned end in order to protect participants’ rights and ensure research quality:

Serious safety issues arising during the study requiring immediate termination.Major errors discovered in the clinical research protocol, making it difficult to evaluate drug efficacy; or important deviations occurring from a well-designed protocol, compromising the efficacy evaluation.Very favorable outcomes observed in the TCM group during the study warranting that the trial be terminated early to allow the control group to receive the TCM treatment.Termination requested by the research team (eg, due to funding or management issues).Termination required by administrative authorities.

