### Study Procedures

Table 1 outlines the specific measurements and timepoints for data collection in this study. Eligible participants will undergo a 1-week preintervention screening period, a 12-week treatment period, and a total 48-week follow-up period. After the study begins, all enrolled participants will have follow-up visits every 12 weeks. All participants will be informed of the study through oral and written information and will be required to sign an informed consent form.

**Table 1 table1:** Clinical trial research timeline.

Item		Screening period and baseline	Visit 1	Visit 2	Visit 3	Visit 4
Visit time		–7 to 0 days	12 weeks ± 7 days	24 weeks ± 7 days	36 weeks ± 7 days	48 weeks ± 7 days

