## Results

The study was approved by the Ethics Committee of Guang’anmen Hospital, China Academy of Chinese Medical Sciences, on March 3, 2025 (2025-025-KY-01), and was registered on the International Traditional Medicine Clinical Trial Registry on April 6, 2025 (ITMCTR2025000653), and any potential protocol amendments will be recorded there. Participant screening began on April 10, 2025, with enrolment expected to be completed by December 31, 2025. The final study results are planned to be published by December 31, 2026.

This study aims to evaluate the efficacy and safety of Qizhi Jieyu pill in the treatment of patients in the recovery phase of cerebral infarction, providing a treatment option supported by high-quality, evidence-based medicine for the clinical management of recovery phase cerebral infarction.

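### The effect-based midterm sample-size reassessment and the unbounded early stop for benefit conflict with a flat .05 test, and week-48 results come too late to guide the sample size within planned recruitment

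*Protocol article*

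**What the plan says.** Three statements in the protocol article bear on this point.

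- **Sample Size Calculation.** A third-party group "will be organized at the midterm of the study" and is "to reassess the sample size based on the observed effect size of the primary efficacy indicators and associated errors". Midterm is not defined by a date, a number enrolled or a fraction of the data.
- **Trial Termination Criteria.** One ground for ending the trial is "Very favorable outcomes observed in the TCM group during the study warranting that the trial be terminated early". It carries no threshold or timing and is not linked to the third-party group.
- **Statistical Analysis Plan.** "All hypothesis tests will be 2-sided, with a significance level of α=.05", and P "values less than or equal to .05 will be considered statistically significant". No exception is made for an interim look or a changed sample size.

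The timing comes from three other places. Under Primary Outcome: "The primary outcome is the change in NIHSS score at 48 weeks". In the visit table under Study Procedures, the last visit is at "48 weeks ± 7 days". Under Results: "Participant screening began on April 10, 2025, with enrolment expected to be completed by December 31, 2025".

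**The concern.** An observed effect size is a between-group quantity, so the reassessment described is comparative, not a blinded check of the variance. Changing the sample size in response to it, or stopping when the study group looks very good, gives chance more than one route to a positive result. A final test at .05 does not in general pay for that. Participants and clinicians know the allocation (Randomization section), which makes an undefined judgement of very favorable results harder to defend.

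There is also a question of timing. The primary outcome is measured almost a year after entry, while recruitment is planned to last under nine months. If the primary effect cannot be seen while recruitment is open, the review cannot do its job within the planned enrolment, and the SD and effect borrowed from other studies go unchecked.

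**Working it through.** **1. The plan's own sample size.** Inputs from Sample Size Calculation: SD 2.0, α .05 two-sided, power .80, control change 4.9, study-group change 6, stated difference 2. With n per group = 2σ²(1.960 + 0.842)²/δ²:

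- δ = 6 − 4.9 = 1.1: 2 × 4 × 7.849 / 1.21 = 51.9, so 52, the published figure.
- δ = 2: 2 × 4 × 7.849 / 4 = 15.7, so 16, which does not match.

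Only 1.1 yields 52, so any reassessment that holds the target fixed must first settle which target is meant.

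**2. Timing.** Inputs: April 10, 2025 start, December 31, 2025 expected close, week 48 = 336 days, window ±7 days.

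| Event | Arithmetic | Date |
|---|---|---|
| Expected close of enrolment | stated | December 31, 2025 |
| Calendar midpoint, start to last week-48 visit | 601 days / 2 | about February 4, 2026 |
| First possible week-48 visit | start + 336 days | March 12, 2026 (March 5 with window) |
| Half the participants past week 48 (even accrual assumed) | enrolment midpoint August 20, 2025 + 336 days | about July 22, 2026 |
| Last week-48 visit | close + 336 days | about December 2, 2026 |

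The first week-48 result comes 71 days after expected close (64 with the window). At close, and at the calendar midpoint, 0 of 126 participants have one. If midterm means half the week-48 data, enrolment has been closed for about 203 days, over six months.

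**3. Error rates under assumed rules.** The article gives no look time, boundary or cap, so these are illustrations. All take the interim at half the information and the final test at two-sided .05.

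- *Look and final test both at .05.* The two z-statistics have correlation √0.5 = 0.707. P(either |z| > 1.96) = 8.3% two-sided (9.1% and 7.3% if the look is at 25% or 75% of the information).
- *Stop for benefit only.* Error in the pill's favour, against a nominal 2.5%: 4.2% with an interim threshold of P<.05, 2.7% at P<.01, about 2.5% at P<.001.
- *Re-estimation to 80% power on the observed effect*, increase only, capped at twice the planned size, no stopping. Simulated under the null with 26 of 52 per group at the interim: 6.0% two-sided, about 3.0% in the pill's favour.
- *Same re-estimation, but increasing only when conditional power under the observed trend is at least 50%*: 4.8% two-sided, so no inflation.

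**4. Week-12 data during recruitment.** Under even accrual over 265 days, participants with week-12 data on a given date = 126 × (days from April 10 to that date less 84 days) / 265. September 30: 126 × 89/265 = 42. October 31: 126 × 120/265 = 57. December 31: 126 × 181/265 = 86.

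**The case against.** **The detail may sit in the SAP.** Boundaries, look times and caps commonly do, and the article says that its text gives only standard requirements. That is fair for the missing detail. It does not remove the conflict: the article states two effect-driven provisions and fixes every test at .05, so an SAP that adjusted the level would contradict the article.

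**Midterm is undefined.** The text speaks of primary efficacy indicators in the plural, and NIHSS is scored at every visit, so week-12 to week-36 scores could be the basis. December 31 is only an expected date, and an increase would extend recruitment. All of this stands. A reader might infer that no week-48 data can exist at the midterm, or that the review cannot work at all. The documents do not support that: the first is untrue if midterm means half the week-48 data, and the second ignores earlier NIHSS scores. What stands is narrower: the week-48 effect cannot inform the sample size within planned recruitment.

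**The inflation depends on an unseen rule.** This also stands. A reader might infer that the type I error certainly exceeds 5%. It need not: very favorable could mean a bar as strict as P<.001, and some re-estimation rules do not inflate error. Nor should four visits be read as four interim tests. Visits are per participant, and the primary outcome exists only at the fourth.

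**The two complaints pull apart.** A review that cannot see the week-48 effect cannot inflate error through it. That is correct, and it is why the error argument is conditional: it applies if the review or the stop uses unblinded effect data, for example from a later look or from correlated earlier NIHSS scores.

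**Conclusion.** The concern holds in limited form and should be fixed. The article's statements on reassessment, early stopping and a flat .05 need to be reconciled. On the stated dates, a reassessment on the week-48 effect comes at least 64 days after expected close, or over six months after it if half the week-48 data are awaited, so it cannot guide the sample size within planned recruitment.

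If either provision is used on unblinded effect data with the final test at .05, the 5% error is not assured. The illustrations run from practically no inflation (strict boundary, or increases only when the trend is promising) to 6.0% and 8.3% two-sided. They rest on assumed rules and on a look at half the information. The July 2026 date and the week-12 counts assume even accrual. The date arithmetic up to the first week-48 visit rests only on the published dates.

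**What to change.** 1. Replace the effect-based reassessment with a blinded reassessment of the pooled SD of NIHSS change at week 12, at a fixed date while recruitment is open. October 31, 2025 would give about 57 participants under even accrual; waiting until the last day of recruitment gives 86, but too late to be useful.
2. Hold the target difference fixed in that reassessment, after reconciling the stated 2 with the 1.1 that reproduces 52 per group.
3. Tie any early stop for efficacy to one prespecified look with an O'Brien-Fleming or Haybittle-Peto boundary, applied by the independent third-party group. For one look at half the information, the O'Brien-Fleming nominal levels are .0052 at the interim and .0480 at the end. Amend the flat .05 statement to match.
4. Leave the safety termination criteria unchanged.

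The cost is wording in the protocol and SAP, plus convening the third-party group earlier, since it is yet to be organized. There are three drawbacks: the week-12 SD is only a proxy for the week-48 SD, the sample size can no longer follow the observed effect, and an early efficacy stop becomes harder to reach.
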